### 2.8. Sample Size

The sample size was determined by the objective of estimating the primary outcome of the study. The standard deviation and expected difference in disease-related QoL between groups for the sample size were based on data from studies of IBD patients assessed with SIBDQ. The standard deviation was taken to be 12.52 points based on the study by Sun et al. [27]. The expected difference between the study groups was chosen to be smaller than the clinically significant change in HRQoL according to Jowett et al. [28] and taken to be 10 points. Considering a potential loss and incomplete records of 20%, a total of at least 64 patients (32 patients in the control group and 32 patients in the intervention group) should be included in the study to detect a difference between groups with a statistical power of 80% (two-sided type I error of 0.05).

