### 2.9. Statistical Methods

The results will be analyzed only after the follow-up of all the included patients has been completed. The questionnaire scores will be calculated based on scoring guides from the questionnaire developers. Missing questions will be processed according to these guidelines. Patients without completed SIBDQ at any study point will be excluded from the analysis. Patients who refused to participate at any point in the study will be excluded from the analysis. We plan to use the full analysis set and the per protocol set (for patients without completed SIBDQ at any study point or who refused to participate at any point in the study).

Continuous variables will be tested for normality using the Shapiro–Wilk test and presented as mean (SD) or median (IQR), as appropriate. Categorical variables will be presented as percentages. For demographic and clinical data, descriptive statistics will be used to characterize the study population and to identify erroneous values. Additionally, missing values will be analyzed to determine the randomness of these omissions.

Hypothesis testing will be conducted for primary and secondary outcomes (Table 4). Quantitative variables will be compared using the Student’s T-test or the Mann–Whitney U test, as appropriate, and qualitative variables will be compared using the Fisher’s exact test. Univariate analysis of variance and multiple linear regression will be performed to analyze the association of secondary outcomes with the primary outcome. The Benjami and Hochberg (BH) false discovery rate (FDR) approach will be used to correct for multiple comparisons (*p* < 0.05). For the variables with FDR ≤ 10%, the term “showing a trend” will be used to avoid confusion with statistically significant variables.

All the analysis will be performed using a Python version of at least 3.7.0 or an R version of at least 4.2.0. A value of *p* < 0.05 will be considered statistically significant.

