Endoscopic activity of CD	Endoscopic activity of CD assessed via colonoscopy	Simple Endoscopic Score for Crohn’s Disease (SES-CD)	0–2—remission; 3–6—mild severity; 7–15—moderate severity; >15—severe;
Histological activity of IBD	Histological activity of IBD assessed via biopsy	Binary scale	No signs of inflammation in the histological material; Presence of signs of inflammation in the histological material
Laboratory tests	White blood cells concentration; Haemoglobin concentration; C-reactive protein concentration; Fecal calprotectin concentration;	Blood test and stool test	Normal values: 4–11 × 10^9^ cells/L; 120–170 g/L; 0–5 mg/L; <200 µg/g for patients with initially normal levels. <800 µg/g in both time-points for patients included in the trial with initially high levels
General medication adherence differences	Adherence to the prescribed medications, interpreted in 5 levels of adherence	GMAS score	0–10—poor adherence; 11–16—low adherence; 17–26—partial adherence; 27–29—good adherence; 30–33—high adherence;
Rate of non-scheduled medical encounters *	Unplanned visits to the Physician for IBD symptoms	As recorded in electronic health record	Number of non-scheduled visits
Rate of surgical interventions *	Surgical interventions for IBD complications	As recorded in electronic health record	Number of surgical interventions
Rate of hospitalizations *	Unplanned hospital admissions for any reason	As recorded in electronic health record	Number of unplanned hospitalizations with specification of the reason

* we assume that telemonitoring will lead to decrease in these parameters.

**Table 4 jcm-13-07734-t004:** Hypotheses proposed according to the primary and secondary study aims.

*Hypothesis*	**H_0_**	**H_a_**	
	6 months after the start of observation, there is no difference between the groups on the evaluated parameter	6 months after the start of observation, the values of the assessed parameter are higher in the telemonitoring group	6 months after the start of observation, the values of the estimated parameter are lower in the telemonitoring group
Outcomes	All primary and secondary outcomes	HRQol Generic QoL General medication adherence Satisfaction with medical care	Clinical activity of UC/CD Rate of leukopenia in patients taking immunomodulators (thiopurines, cyclosporine, tacrolimus) Depression and anxiety Visceral sensitivity Alexithymia

H_0_—null hypothesis; Ha—alternative hypothesis.

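### The decision rule for the primary outcome is stated inconsistently; if SIBDQ is inside the Benjamini-Hochberg family, the trial does not keep its stated 80% power

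*Protocol article*

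**What the plan says.** Three places in the protocol article bear on how the primary outcome, SIBDQ at 6 months, will be judged.

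- **Section 2.8 (Sample Size)** sizes the trial on SIBDQ alone, "to detect a difference between groups with a statistical power of 80% (two-sided type I error of 0.05"). No part of that alpha is shared with another outcome.
- **Section 2.9 (Statistical Methods)** states "Hypothesis testing will be conducted for primary and secondary outcomes (Table 4"). After a sentence on association analyses it continues: "The Benjami and Hochberg (BH) false discovery rate (FDR) approach will be used to correct for multiple comparisons", with 0.05 as the threshold. Variables with an FDR of up to 10% are to be described as a trend. The section closes with a general 0.05 significance level and does not say whether it applies to raw or adjusted p-values.
- **Table 4** sets one null of no difference for the primary and all secondary outcomes. Its alternatives are all directional. Disease-related quality of life stands under "6 months after the start of observation, the values of the assessed parameter are higher in the telemonitoring group". No outcome has an alternative in the unfavourable direction.

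**The concern.** A trial with one primary outcome needs one rule for declaring it positive. Here the same SIBDQ result can lead to different conclusions depending on which section the analyst follows.

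Take a two-sided SIBDQ p-value of 0.03 and assume a family of 10 tests. Under section 2.8 it is significant. Inside a Benjamini-Hochberg (BH) family:

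- If the other nine p-values all exceed 0.30, the adjusted value is 0.03 × 10/1 = 0.30, which is not significant.
- If SIBDQ ranks fourth and the remaining p-values are large, it is 0.03 × 10/4 = 0.075, which the protocol would label a trend.
- If all ten p-values are at or below 0.03, it is at most 0.03, which is significant.

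The quality-of-life conclusion would then depend on results such as visceral sensitivity or alexithymia. The sample size makes no allowance for this. If the rule stays open until the data are seen, the more favourable one can be chosen afterwards.

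Table 4 raises a second, separate question. A two-sided test has a two-sided alternative, and Table 4 does not give one.

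**Working it through.** **Inputs.** From section 2.8: "The standard deviation was taken to be 12.52 points", the expected difference was "taken to be 10 points", power 80%, two-sided alpha 0.05, 20% loss, 32 patients per arm. The number of tests, m, is an assumption because the family is not defined. Table 3 has 1 primary and 9 secondary rows, so m = 10. Counting the four WHOQOL domains and the two HADS scales separately gives m = 10 + 3 + 1 = 14.

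**Step 1: reproduce the stated sample size** (normal approximation).

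n per arm = 2 × [12.52 × (1.960 + 0.842)/10]² = 24.6, rounded up to 25. After 20% loss, 25/0.8 = 31.25, rounded up to 32 per arm, or 64 in total. This matches. One-sided 0.05 would give 20 per arm, 20/0.8 = 25 after loss, and 50 in total, which does not match. The planned 64 therefore rests on an unadjusted two-sided 0.05 test.

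**Step 2: power at fixed thresholds, 25 completers per arm.**

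Noncentrality = 10/(12.52 × √(2/25)) = 2.824. Power ≈ Φ(2.824 − critical value).

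| Rule for SIBDQ | Critical value | Power |
|---|---|---|
| Two-sided 0.05, unadjusted | 1.960 | 80.6% |
| Strictest BH step, m = 10 (0.05/10 = 0.005) | 2.807 | 50.7% |
| Strictest BH step, m = 14 (0.05/14 = 0.0036) | 2.914 | 46.4% |
| One-sided 0.05 | 1.645 | 88.1% |

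With the t distribution the first three rows are lower, at 79.0%, 46.1% and 41.5%. The comparisons below stay on the normal scale throughout.

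**Step 3: power under BH itself.** The threshold for SIBDQ moves between 0.05/m and 0.05 with the other results, so BH was simulated: 40,000 runs per setting, 25 per arm, m = 10 or 14, common correlation between tests of 0, 0.3 or 0.5. The standardized effect on SIBDQ is 10/12.52 = 0.80 SD.

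| Assumed true effects on the secondaries | Power for SIBDQ |
|---|---|
| None | 47-51% |
| All have half the primary's effect | 53-61% |
| About half share the primary's effect | 65-68% |
| All share the primary's effect | 75-78% |

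Using 32 × 0.8 = 25.6 completers per arm, and correlations of 0 or 0.4, the first row becomes 48-53% and the last 76-79%, against 81.5% unadjusted. Over both versions the range is about 47-53% to 75-79%, against 80-82% unadjusted.

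**Step 4: what the strictest step would cost in patients.** 80% power at 0.05/m needs 42 per arm (m = 10) or 45 (m = 14). Divided by 0.8 and rounded up, this is 53 or 57 per arm, or 106 or 114 in total, against 64 planned.

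**Step 5: the Table 4 wording.** A two-sided 0.05 test allows 2.5% false positives in favour of telemonitoring. A one-sided 0.05 test in the direction of Table 4 would allow 5%. Its power would be higher (88.1%), so this part concerns type I error only.

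**The case against.** The strongest reply is that nothing in the protocol expressly puts the primary in the BH family. The BH sentence directly follows the one on analysis of variance and regression, which generate many tests. Section 2.8 gives SIBDQ its own two-sided 0.05. A reading with the primary at 0.05 and BH for everything else fits both sections, and under it the 80% stands. The exact family could also be left to an analysis plan that is not shown. This makes the power loss conditional. It does not remove the inconsistency: section 2.9 names primary and secondary outcomes together, points to a table that pools them, and then corrects without exempting any of them.

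A reader might infer from Table 4 that a one-sided test is planned, that a harmful effect would go untested, or that the directional wording itself costs power. The protocol does not support this. The only sidedness it states is two-sided, the null is no difference, and the directions match the expectations in the Introduction and in section 3.2. They may be no more than that. A one-sided test would in any case raise power. What stands is that Table 4 labels these directions as formal alternatives, and so does not match section 2.8.

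Nor does the closing 0.05 sentence in section 2.9 clearly contradict the BH rule, since it can be read as applying to adjusted p-values.

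The simulated settings are also stylized. DAI applies only to ulcerative colitis, CDAI only to Crohn's disease, and leukopenia only to immunomodulator users, so equal effects at full sample size do not describe the real family. The case of no secondary effects runs against the trial's own hypotheses. For that reason the range is shown up to the favourable end, where the loss is only a few percentage points.

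**Conclusion.** The point holds as a conflict between stated rules, with a conditional effect on power. The sample size arithmetic is correct for its own inputs, so it would be wrong to say outright that the 80% fails. It fails if the primary is corrected together with the secondaries, which is the most natural reading of section 2.9 with Table 4. Power was below the unadjusted figure in every such setting examined. The size of the loss rests on the assumed m of 10 to 14, the assumed correlations, about 25 completers per arm and the assumed secondary effects. It ranges from a few points to about 30 points or slightly more.

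The mismatch between Table 4 and the two-sided test is a lesser matter of wording. It would affect the error rate only if someone acted on it with a one-sided 0.05 test, which the protocol does not specify.

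**What to change.** - **Section 2.9:** state that SIBDQ at 6 months is tested alone, two-sided, at 0.05, outside any multiplicity correction.
- **Section 2.9:** state that BH at 5% is applied only within the secondary outcomes of Table 3, list the tests in that family (including whether WHOQOL domains and HADS scales count separately), and judge these outcomes on BH-adjusted p-values. Limit the closing 0.05 sentence accordingly.
- **Table 4:** replace the directional alternatives with two-sided ones and keep the expected direction as a remark.

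The cost is a few sentences and a change to the Table 4 alternatives, made before any outcome data are seen. No extra patients are needed, and the 64 patients and 80% power stand as calculated. If the sponsor instead wants the primary inside the BH family, the sample size must be recalculated for that rule.

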## 3. Discussion

### 3.1. Overview

In this article, we describe the key elements of the design of a randomized control study aimed to evaluate telemonitoring efficacy for IBD in Russia.

The available evidence has shown that IBD patients have a lower quality of life compared to healthy individuals [29], even during periods of remission [30]. IBD is characterized by a relapsing and remitting clinical course that requires lifelong monitoring. Telemonitoring offers a promising solution by enabling the continuous monitoring of a wide range of health-related parameters. A recent systematic review has indicated that telemonitoring improved the QoL for individuals with IBD [11]. However, the systematic review of Nguyen et al., which employed the GRADE (Grading of Recommendations, Assessment, Development, and Evaluations) approach, showed a reduction in healthcare utilization and costs, with no change in QoL, disease activity, or medical adherence (low or very low certainty of evidence) [31].

These results highlight the need for further studies to better understand the true impact of telemonitoring on IBD patients. The studies included in the reviews assessed various parameters and used different metrics, which shows the complexity of evaluating telemonitoring in IBD. To address this complexity, we decided to evaluate the impact of telemonitoring on a broad range of parameters, including clinical, social, and organizational aspects (see Table 1). Previously, we approached the issue systematically and surveyed gastroenterologists specializing in IBD treatment. Thus, we determined the parameters that should be monitored in IBD patients during telemonitoring [13]. It is important to note that this is the first trial in Russia aimed to evaluate telemonitoring efficacy in IBD.

When considering the scalability of an intervention, we can hypothesize that telemonitoring might be a suitable option for IBD patients in remote areas who do not have direct access to qualified face-to-face medical care. After the study completion, we plan to use the Intervention Scalability Assessment Tool (ISAT) [32] for the scalability assessment. In Russia, there are already examples of telemonitoring being implemented at the state level, such as the Federal project ‘Personal Medical Assistants’ https://ppma.ru/, which provides remote monitoring for patients with type 2 diabetes and arterial hypertension, funded by compulsory medical insurance.

### 3.2. Expected Findings

We anticipate that the implementation of TMT in monitoring patients with IBD will improve their QoL. This will be achieved through a reduction in overall and visceral anxiety, as well as constant, immediate access to medical care. Additionally, we expect an increase in satisfaction with medical care, improved psychological well-being, and a decrease in disease activity and relapse rate due to timely response and improved adherence to treatment.

### 3.3. Strengths

This study has been designed in close collaboration with patients to ensure that it addresses their specific needs and concerns. We discovered that there is a lack of standardized criteria for evaluating patients with IBD during monitoring except for objective markers of disease activity. We defined the list of assessed parameters by the Delphi method before the trial [13]. Another advantage of this trial is that the protocol has been developed in accordance with the SPIRIT guidelines, which will improve its transparency [14].

### 3.4. Limitations

The study has some limitations. One potential limitation is an uneven distribution of patients with UC and CD within the groups. Due to envelope randomization, there may be differences in the number of participants with UC or CD between the face-to-face and telemonitoring groups. Furthermore, the study does not intend to perform subgroup analysis based on a specific disease, such as UC or CD.

Another limitation of this study is that it is a single-center study. Different hospitals may have slightly different approaches to face-to-face management of patients. Additionally, patients in the groups may differ in the activity and severity of their IBD course, which could impact the therapy they receive during the study period.

Furthermore, the use of a website as a telemedicine intervention may also be a limitation. This approach requires patients to have certain technical equipment and computer literacy, which could reduce the number of study participants.

## 4. Conclusions

Our study aims to assess the effects of telemonitoring on patients with IBD in comparison to traditional face-to-face follow-up. Specifically, we will evaluate the impact on various aspects, such as QoL, frequency of disease relapses, medication adherence, adverse drug reaction of immunomodulators, and satisfaction with medical care.

## Figures and Tables

**Figure 1 jcm-13-07734-f001:**
[figure not shown]
Study design.

**Figure 2 jcm-13-07734-f002:**
[figure not shown]
An online platform structure for patients in the intervention group.

**Table 1 jcm-13-07734-t001:** Summarizes the trial interventions and participant timeline.

	Study Period						
	Enrolment/Baseline 0 Weeks	Follow-Up					End of the Study (6 Months)
		1 Month	2 Months	3 Months	4 Months	5 Months	
Informed consent	X						
Eligibility criteria	X						
Demographic data	X						
Treatment in the Gastroenterology Department	X						X
Adverse events		X	X	X	X	X	X
Treatment	X	X	X	X	X	X	X
Face-to-face consultation for both groups	X						X
Observation using telemedicine technologies for the intervention group (including web-platform, phone calls)		X	X	X	X	X	
Clinical parameters							
Haemoglobin concentration	X	X	X	X	X	X	X
White blood cells concentration	X	X	X	X	X	X	X
C-reactive protein concentration	X			X			X
Fecal calprotectin concentration	X			X			X
IBD disk		X	X	X	X	X	
HBI/SCCAI questionnaire	X	X	X	X	X	X	X
Disease severity according to laboratory and instrumental data	X						X
Disease severity according to CDAI/UCDAI	X						X
Social parameters							
VSI questionnaire	X						X
TAS-26 questionnaire	X						X
HADS questionnaire	X						X
SIBDQ questionnaire	X						X
WHOQOL-26 questionnaire	X						X
Organizational parameters							
PSQ-18 questionnaire	X						X
GMAS questionnaire	X						X

**Table 2 jcm-13-07734-t002:** Limit values of the laboratory tests.

Laboratory Parameter	Critical Deviation from Reference Values
Haemoglobin concentration	Lower than 110 g/L; higher than 170 g/L
White blood cells concentration	Lower than 3 × 10^9^ cells/L; higher than 11 × 10^9^ cells/L
C-reactive protein concentration	Higher than 10 mg/L
Fecal calprotectin concentration	Higher than 200 µg/g for patients included in the trial with initially normal levels. Maintaining the level of more than 800 µg/g between two time points (Table 1) for patients included in the trial with initially high levels

**Table 3 jcm-13-07734-t003:** Study outcomes and data collection methods.

Item	Definition	Data Collection Method	Measure
Primary outcome			
Health-related quality of life (HRQol) in IBD	QoL specifically associated with bowel symptoms	SIBDQ score	Min score is 10, max score is 70. <50 means poor HRQol; >50 optimal HRQol Higher score means better outcome
Secondary outcomes			
Generic QoL	Generic QoL associated with several domains of life quality (physical and mental health, social relationships, and environment)	WHOQOL-26 score	Min score is 0%, max score is 100% for each domain. Higher score means better outcome.
Clinical activity of UC	Clinical activity of UC according to DAI with questions regarding clinical symptoms and endoscopic activity	DAI	0–2—remission; 3–6—mild activity; 7–10—moderate activity; >10—severe activity;
Clinical activity of CD	Clinical activity of CD according to CDAI, which is a ‘gold standard’ for trials. CDAI consists of questions regarding symptoms, lab tests, extraintestinal complications, general well-being	CDAI	<150—remission; 150–300—mild activity; 301–450—moderate activity; >450—severe activity;
General medication adherence	Adherence to the prescribed medications, patient compliance	GMAS score	0–26—non-adherent; 27–33—adherent [26];
Rate of leukopenia in patients taking immunomodulators (thiopurines, cyclosporine, tacrolimus)	Leukopenia that is associated with the intake of immunomodulators according to full blood count during the monitoring	Electronic health record, full blood count	Number of patients taking immunomodulators with onset of leukopenia
Satisfaction	Patient satisfaction with healthcare	PSQ-18 score	Min score is 18, max score is 90. Higher score means better outcome;
Depression and anxiety	Levels of anxiety and depression in patients with chronic diseases	HADS	The HADS has two scales: for anxiety (HADS–A) and for depression (HADS–D), differentiating the two states. For each scale: 0–7—no depression or anxiety; 8–10—a doubtful case; 11–21—a definitive case;
Visceral sensitivity	Gastrointestinal (GI) symptom-specific anxiety causing bowel symptoms persistence	VSI score	0–10—no GI-specific anxiety; 11–30—moderate GI-specific anxiety; 31–75—severe GI-specific anxiety;
Alexithymia	Difficulty to perceive and express emotions	TAS-26 score	26–62—no alexithymia; 63–74—a doubtful case; 75–130—a definitive case;
Additional outcomes			
Endoscopic activity of UC	Endoscopic activity of UC assessed via colonoscopy	Mayo Endoscopic Score (MES)	0—normal or inactive disease; 1—mild disease with erythema, decreased vascular patterns and mild friability; 2—moderate disease with marked erythema, absence of vascular patterns, friability and erosions; 3—severe disease with spontaneous bleeding and ulceration
Endoscopic activity of CD	Endoscopic activity of CD assessed via colonoscopy	Simple Endoscopic Score for Crohn’s Disease (SES-CD)	0–2—remission; 3–6—mild severity; 7–15—moderate severity; >15—severe;
Histological activity of IBD	Histological activity of IBD assessed via biopsy	Binary scale	No signs of inflammation in the histological material; Presence of signs of inflammation in the histological material
Laboratory tests	White blood cells concentration; Haemoglobin concentration; C-reactive protein concentration; Fecal calprotectin concentration;	Blood test and stool test	Normal values: 4–11 × 10^9^ cells/L; 120–170 g/L; 0–5 mg/L; <200 µg/g for patients with initially normal levels. <800 µg/g in both time-points for patients included in the trial with initially high levels
General medication adherence differences	Adherence to the prescribed medications, interpreted in 5 levels of adherence	GMAS score	0–10—poor adherence; 11–16—low adherence; 17–26—partial adherence; 27–29—good adherence; 30–33—high adherence;
Rate of non-scheduled medical encounters *	Unplanned visits to the Physician for IBD symptoms	As recorded in electronic health record	Number of non-scheduled visits
Rate of surgical interventions *	Surgical interventions for IBD complications	As recorded in electronic health record	Number of surgical interventions
Rate of hospitalizations *	Unplanned hospital admissions for any reason	As recorded in electronic health record	Number of unplanned hospitalizations with specification of the reason

* we assume that telemonitoring will lead to decrease in these parameters.

**Table 4 jcm-13-07734-t004:** Hypotheses proposed according to the primary and secondary study aims.

*Hypothesis*	**H_0_**	**H_a_**	
	6 months after the start of observation, there is no difference between the groups on the evaluated parameter	6 months after the start of observation, the values of the assessed parameter are higher in the telemonitoring group	6 months after the start of observation, the values of the estimated parameter are lower in the telemonitoring group
Outcomes	All primary and secondary outcomes	HRQol Generic QoL General medication adherence Satisfaction with medical care	Clinical activity of UC/CD Rate of leukopenia in patients taking immunomodulators (thiopurines, cyclosporine, tacrolimus) Depression and anxiety Visceral sensitivity Alexithymia

H_0_—null hypothesis; Ha—alternative hypothesis.

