Patients will be required to log in to the web platform at least once per month. Upon logging in, they will need to provide the following information: (1) SCCAI for ulcerative colitis and the Harvey-Bradshaw index for Crohn’s disease to assess disease activity during monitoring; (2) the IBD disk questionnaire to track disease progression; and (3) results from laboratory tests (complete blood count, C-reactive protein, and fecal calprotectin). Both healthcare professionals and patients will have access to the test results. Additionally, patients can request an online consultation with a gastroenterologist via chat or phone call. They will be advised to contact a gastroenterologist if they experience disease recurrence.

Each month, gastroenterologists will call patients in the intervention group and ask questions based on a checklist (Multimedia Appendix A). They will be trained to provide immediate assistance if there are critical deviations in health indicators from the reference values (see Table 2) or complaints suggesting the onset of an acute condition.

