##### Web Platform Description

Web platform http://ondoc.telemedai.ru/ provides access to a personal patient profile, a newsfeed with educational information (Appendix F, Figure A1), chat with the gastroenterologist (Appendix F, Figure A2), a health parameters monitoring page (Appendix F, Figure A3), information about the gastroenterologist (Appendix F, Figure A4), and the questionnaires module (Appendix F, Figure A5).

#### 2.5.3. Stage 3

After six months of monitoring, participants from both groups will be readmitted to the hospital. IBD activity will be assessed through laboratory and instrumental tests, including a complete blood count, C-reactive protein levels, fecal calprotectin, colonoscopy with biopsy, and computed tomography or MR-enterography (for patients with severe IBD or jejunoileitis). Both groups will also have to recomplete all the questionnaires to evaluate the study endpoints (see Table 1).

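### On the Table 1 schedule, the Table 2 calprotectin criterion cannot be met during telemonitoring by patients who enter between 200 and 800 µg/g

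*Protocol article*

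**What the plan says.** Section 2.5.2 (Stage 2) has the telemonitoring gastroenterologists trained to help at once when there are "critical deviations in health indicators from the reference values (see Table 2"), or when complaints suggest an acute condition. Table 2 is thus an operating rule of the intervention.

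For calprotectin, Table 2 gives two criteria:

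- The first applies "for patients included in the trial with initially normal levels" and is met by one value above 200 µg/g.
- The second requires a level that stays above 800 µg/g "between two time points (Table 1) for patients included in the trial with initially high levels".

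Table 1 fixes the measurement times. The row "Fecal calprotectin concentration X X X" has its marks at baseline, month 3 and month 6. The row "Observation using telemedicine technologies for the intervention group (including web-platform, phone calls") is marked at months 1 to 5 and not at month 6. Section 2.5.3 explains month 6: "After six months of monitoring, participants from both groups will be readmitted to the hospital".

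Three further places bear on the point:

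- Table 3 gives the normal calprotectin value as below 200 µg/g for patients normal at entry, and below 800 µg/g at both time points for patients high at entry. Neither table gives a numeric lower bound for the high class.
- Sections 2.2.1 and 2.2.2 set no calprotectin condition for entry.
- Section 2.5.2 requires a login at least once a month, and calprotectin is among the laboratory results to be entered at login.

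**The concern.** Table 2 names two classes of patient but defines neither by a number. Table 3 implies that normal is below 200 µg/g. The only figure attached to the high class is 800 µg/g, and that is a limit for later values, not an entry bound. Patients entering between 200 and 800 µg/g are eligible, and they sit in the space between the two figures.

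The high-class criterion also needs two time points, while Table 1 places only one calprotectin result inside the telemonitoring period. A patient who starts at or below 800 µg/g cannot use the baseline value as one of the pair.

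At stake is whether this part of the intervention can work as written for every eligible patient, and whether it is delivered alike to all of them. Section 3.2 expects part of the benefit on disease activity and relapse to come from timely response, so an alert that cannot be reached matters for safety monitoring and for describing what was tested.

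**Working it through.** The plan gives no computed figure on this point, so there is none to reproduce. The check applies the rule to the schedule.

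**Inputs**

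- Calprotectin times in Table 1: 0, 3 and 6 months.
- Telemonitoring in Table 1: months 1 to 5.
- Normal-entry criterion in Table 2: one later value above 200 µg/g.
- High-entry criterion in Table 2: two successive time points above 800 µg/g.
- Normal at entry: below 200 µg/g (implied by Table 3).
- High at entry: undefined, so read both as 200 or more and as above 800.
- Alternative schedule in section 2.5.2: at least monthly.

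**Test case.** Calprotectin jumps to 5000 µg/g at the first measurement after baseline and stays there. This is the case most favourable to an alert, so the result is the earliest month at which the criterion can be met.

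| Entry level (µg/g) | Reading of high | Table 1 schedule | Monthly schedule |
|---|---|---|---|
| below 200 | either | month 3 | month 1 |
| 200 to 800 | 200 or more | month 6 | month 2 |
| 200 to 800 | above 800 | no class, never | no class, never |
| above 800 | either | month 3 | month 1 |

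**Step by step on the Table 1 schedule**

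1. Entry 900, month 3 850: both values exceed 800, so the criterion is met at month 3, inside the window.
2. Entry 190, month 3 201: one value above 200 suffices, so it is met at month 3.
3. Entry 300, month 3 1500, with high read as 200 or more: baseline is not above 800, so the pair 0 and 3 fails. The next pair is 3 and 6, and month 6 is the readmission, after the last month marked for telemonitoring.
4. The same patient with high read as above 800: 300 is neither below 200 nor above 800, so no criterion applies at any time.

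For entry between 200 and 800 µg/g, month 3 is the only scheduled result inside the window, and no value at month 3 can meet the criterion under either reading.

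**On the monthly schedule** the first possible pair is months 1 and 2, so an alert could fire at month 2. This needs high to mean 200 or more, and monthly entries to count as time points although Table 2 refers to Table 1 for them.

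**Table 3 against Table 2.** A value of 1500 at month 3 is outside the normal range that Table 3 gives for patients high at entry, yet it is not a critical deviation under Table 2 for the patient in step 3. The two tables do not line up for this group.

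**The case against.** The strongest reply is that section 2.5.2 asks for calprotectin at least monthly, so the criterion can be met early. This stands in part. It shows that the finding depends on which schedule governs, and it reveals a conflict between section 2.5.2 and Table 1. It does not remove the gap: Table 2 itself points to Table 1, and if high means above 800 the gap remains on either schedule.

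A second reply is that other safeguards run throughout, and this stands in full. Table 2 also has limits for C-reactive protein, haemoglobin and white cells. HBI or SCCAI is completed monthly, the call checklist in Appendix B asks about stool frequency, blood, weight loss and fever, and patients can make contact themselves. Clinicians can see the results. A reader might infer that a large calprotectin rise would go unnoticed in these patients; the documents do not support that. What is missing is one formal trigger.

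A third reply is that different triggers for different entry levels are a legitimate design. That also stands. A reader might set a rise from 190 to 201, which triggers, against one from 300 to 1500, which does not by month 3, and call the rule self-contradictory. A baseline-dependent rule is not a contradiction, and where its limits sit is a clinical choice. The defect is that the classes are not exhaustive or that the criterion cannot be reached in time, depending on the reading.

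**Conclusion.** The point holds in a bounded form. On the schedule that Table 2 cites, patients entering between 200 and 800 µg/g cannot meet the formal calprotectin criterion during telemonitoring, under either reading of the high class. The result rests on Table 1 governing the time points and on normal meaning below 200 µg/g, which Table 3 implies and no passage states outright as an entry cut-off. Under monthly entry an alert from month 2 is possible, on the two conditions given above.

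The size in patients is unknown. The documents give no distribution of entry calprotectin, so any count among the 32 planned telemonitoring patients would be a guess. A reader might also infer a weaker contrast between arms on disease activity; nothing in the documents allows that to be quantified. The primary outcome is SIBDQ, and neither its analysis nor the sample size depends on this rule. It should be corrected because a stated operating rule does not work for an eligible group, and correcting it is cheap.

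**What to change.** Reconcile Table 1, Table 2, Table 3 and section 2.5.2 so that:

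- there is one calprotectin schedule, with a statement of whether results entered at login count as time points for the Table 2 criterion;
- the normal and high classes are defined numerically, and every entry level, including 200 to 800 µg/g and the boundary values, falls in exactly one class;
- each class has a criterion that can be met by a result available before telemonitoring ends;
- Table 3's normal ranges and Table 2's critical deviations use the same classes and the same time points.

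The limits themselves are for the investigators to set. The cost is a wording amendment across the three tables and section 2.5.2. It requires no added tests if the Table 1 schedule is kept. The downside is possibly somewhat more alerts for the gastroenterologists to handle.
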